**Discussion:**

The study is expected to provide preliminary evidence regarding the efficacy, safety, and usefulness of EA-CCR for the treatment of MCI.

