### Incidence of adverse events

Adverse events (AEs) are undesirable and unintentional signs, symptoms, or diseases that appear during or after treatment in a clinical trial. The participants in this study will be required to voluntarily report any AEs. All AEs that occur during the trial will be documented. Possible AEs include skin irritation; bleeding; local hematoma; pallor, sweating or dizziness; fainting during EA treatment; needle retention after treatment; continuous severe pain for > 1 h after EA; objective worsening of existing symptoms; and undesirable and unintentional signs, symptoms, or diseases. The CRC will record all AEs in detail, including the time and date of occurrence, degree of severity, any measures related to treatment of the AE, and any potentially causal relationship between the treatment and the AE, and will report all AEs to the PI and relevant IRB. In case of SAEs, defined as those causing severe disability or malfunction, appropriate measures will be taken, and the incident will be immediately reported to the PI and relevant IRB. In case an AE occurs because of the clinical trial, participants will notify the CRC and PI and will be compensated.

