### Statistical analysis

A statistician who is not involved in the clinical trial will analyze the final data. We will perform a per-protocol analysis (PP group) for the assessment of efficacy with a supplementary full analysis set (FA group). We will compare the results of analyses between the PP and FA groups and confirm whether there are statistically significant differences between the two groups. If there is a significant difference, the cause will be reviewed and reflected in the efficacy assessment. All statistical analyses will be performed using SPSS version 21 software (IBM Corp.).

Baseline characteristics will be described and compared. Continuous data will be presented as means and standard deviations and compared using the independent *t* test or Wilcoxon rank sum test, while categorical data will be presented as frequencies and percentages and compared using the chi-squared test or Fisher’s exact test.

Changes in scores for the ADAS-K-cog, MoCA-K scale, CES-D, K-ADL scale, K-IADL scale, and EQ-5D-5 L at 8 weeks (at the end of the intervention) and 20 weeks (12 weeks after the end of the intervention), relative to the baseline score, will be analyzed for each group using the paired *t* test or Wilcoxon signed rank test. The degree of changes at each time point will be evaluated using repeated measures analysis of variance and the two-sample *t* test or Wilcoxon rank sum test. Subanalyses will be applied to the statistical analysis according to the participant age. All reported *P* values will be two-sided with confidence intervals at the 95% levels. A *P*value of < 0.05 will be considered statistically significant.

Data for participants who meet the dropout criteria (i.e., < 75% compliance with the protocol procedures [received less than 18 of the 24 scheduled treatment sessions], incidence of SAEs, reluctance to continue the trial, incomplete data that could influence the trial, large error in protocol or significant deviation in implementation, or decision to terminate trial participation by the PI or IRB) will be excluded. Missing values will be implemented by the last observation carried forward method. Interim analyses will not be performed.

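### The SAE definition leaves out death, life-threatening events and hospital admission, and data of participants with an SAE are excluded with no stated limit

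*Protocol article*

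**What the plan says.** Two rules in the protocol article matter here.

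**Definition and reporting.** The section Incidence of adverse events states "In case of SAEs, defined as those causing severe disability or malfunction, appropriate measures will be taken", and continues that "the incident will be immediately reported to the PI and relevant IRB". The same section sets a wider net for adverse events in general: "All AEs that occur during the trial will be documented". The research coordinator notes timing, severity, measures taken and possible causality, and "will report all AEs to the PI and relevant IRB". The Blinding section adds a second use of the SAE label: unblinding is otherwise forbidden, but may follow an SAE if the researchers agree.

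**Exclusion.** The Statistical analysis section makes PP the main efficacy analysis and FA a supplement. Its last paragraph lists the dropout criteria, among them "incidence of SAEs, reluctance to continue the trial, incomplete data that could influence the trial", and says that the data of participants who meet any of them will be left out. It does not say from which set, or whether only efficacy data are meant.

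The abstract expects the trial to yield "preliminary evidence regarding the efficacy, safety, and usefulness of EA-CCR for the treatment of MCI".

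**The concern.** The definition is worded as a definition, not as an example. Taken at its word, it does not cover the gravest events that can happen to participants aged 55 to 85 during follow-up to week 20 (8 weeks of treatment plus 12). The rules that hang on the label then fail to operate for those events.

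The exclusion is a separate fault. An SAE occurs after randomisation and may be caused by treatment. Dropping participants because they had one makes membership of the analysis set depend on an outcome. If such participants tend to do worse, dropping them flatters the arm with more SAEs. Because the sentence names no set, it may reach the FA analysis, which is there to test whether the PP result depends on who was dropped. Read without limit, it would reach the safety data as well.

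**Working it through.** The documents give no SAE rate, standard deviation or effect size, so there is no stated figure to reproduce. The check compares the texts and then adds three illustrations.

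**1. What depends on the SAE label**

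| Rule (section) | Severe disability or malfunction | Death, life-threatening event or admission, on the words |
|---|---|---|
| Recorded with severity and causality, reported to PI and IRB (Incidence of adverse events) | yes | yes, as an AE |
| Immediate report to PI and IRB (same section) | yes | not required |
| Unblinding may be agreed (Blinding) | yes | not provided for |
| Dropout criterion, data excluded (Statistical analysis) | yes | not on this ground |

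The loss is therefore in classification and speed, not in capture. The unblinding row matters least, since the Discussion says that practitioners and participants know the allocation anyway.

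**2. What the exclusion does on each reading**

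- *PP only.* The main efficacy analysis drops randomised participants because of a possible effect of treatment. FA still holds them.
- *PP and FA.* FA loses the same participants and cannot show whether their removal mattered.
- *All data.* The SAE count among those analysed is zero by construction.

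**3. Size**

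*Efficacy.* Let an arm have n = 18 (Sample size estimation), let k participants be dropped for an SAE, and let their mean change differ by d from that of the other n − k. The full-arm mean is [(n − k)·m + k·(m − d)]/n = m − k·d/n, while the arm mean after exclusion is m. The shift is k·d/n: d/18 = 0.056d for k = 1, 0.111d for k = 2 and 0.167d for k = 3. The documents do not supply d.

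*Safety, on the all-data reading only.* Exact (Clopper-Pearson) 95% limits for x events in n are the 2.5% point of Beta(x, n − x + 1) and the 97.5% point of Beta(x + 1, n − x). For x = 0 the lower limit is 0 and the upper is 1 − 0.025^(1/n).

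| Assumed SAE participants in one arm | All 18 kept | After exclusion |
|---|---|---|
| 1 | 1/18 = 5.6% (0.1 to 27.3%) | 0/17 = 0% (0 to 19.5%) |
| 2 | 2/18 = 11.1% (1.4 to 34.7%) | 0/16 = 0% (0 to 20.6%) |
| 3 | 3/18 = 16.7% (3.6 to 41.4%) | 0/15 = 0% (0 to 21.8%) |

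*Chance that the rule is used at all.* With an assumed SAE probability p per participant, P(at least one among 36) = 1 − (1 − p)^36. This is about 30% for p = 1%, 52% for p = 2%, 84% for p = 5% and 98% for p = 10%.

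**The case against.** The case against is strong on consequences.

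- **Nothing need be missed.** All AEs are documented, graded and sent to the PI and IRB, so a death or an admission would still be on file. This stands, and it limits the first fault to the label, the immediate report and the unblinding route.
- **Deletion of safety data is not a stated rule.** A reader might infer that the plan would report 0/17. The exclusion sentence, however, follows the efficacy sets and the tests on the outcome scales, and no text says that AEs are tabulated after exclusions. This stands: 0/17 is one literal reading of an unlimited sentence.
- **PP only may be what was meant.** The article plans to compare PP with FA, which would show little if both sets lost the same people. This is a fair inference, but the text does not say it, and PP is the main analysis, so the bias remains on that reading.
- **An article condenses.** The trial claims compliance with Korean good clinical practice and has ministry approval, and the full protocol may hold a fuller definition. That is possible, but the published sentence is a stated definition, not an omission.
- **The intervals overlap heavily.** 0 to 19.5% and 0.1 to 27.3% are not distinguishable, and a pilot of this size cannot settle safety. This stands. The point is a biased count, not a reversed conclusion.

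Two further inferences are tempting and are not made here. The lack of a described safety set is detail that an article may leave to the full protocol. The sentence "The participants in this study will be required to voluntarily report any AEs" suggests passive capture in people with memory impairment, but several listed events would be seen by staff, the coordinator monitors participants' medical condition (though the stated purpose is adherence), and the operating procedures are not shown.

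**Conclusion.** The concern holds in two limited parts. First, the SAE definition, on its words, leaves the gravest events outside the label that triggers immediate reporting and permitted unblinding, although they remain recorded and reported as AEs. Secondly, the exclusion for an SAE has no stated scope. On every reading it removes randomised participants from the main PP comparison for an event that treatment may cause; if it extends to FA, it also disables the check on PP.

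The efficacy shift is modest for a single case (one eighteenth of the difference between the dropped participant and the rest) and grows in proportion to the number dropped. It becomes a bias between arms when SAEs, or the outcomes of those who have them, differ by arm. The loss of SAEs from the safety count rests wholly on the all-data reading and on assumed event counts. The documents do not support a statement that the trial will miss serious events or will delete its safety data.

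**What to change.** 1. In Incidence of adverse events, widen the SAE definition to include death, life-threatening events and new or prolonged hospitalisation alongside disability, and tie immediate reporting to the widened definition. The unblinding provision then follows the same label.
2. In Statistical analysis, remove the occurrence of an SAE as a ground for excluding data. If it is kept, restrict the dropout exclusions to the PP set and keep these participants in FA. In either case, state that AEs and SAEs are reported by arm for all treated participants.

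The two changes should be made together: widening the definition alone would bring more participants under the present exclusion.

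The cost is amendment wording, with the ministry and IRB approval that the Quality assurance section requires for any revision. No visit or measurement is added. Reported SAE counts may rise.

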### Quality assurance

This protocol has been reviewed and revised several times by experts on acupuncture, rehabilitation, neurology, statistics, and methodology. Before the trial, all researchers will be required to attend a series of training sessions which will ensure that the involved personnel fully understand the trial protocol and standard operating procedures (SOPs) that will be employed during the study. The Data Monitoring Committee will comprise the PI and CRC. The clinical trial will be monitored by a clinical research associate (CRA) who will check all documents related to the clinical trial, including the case report forms (CRFs) and SOPs, and ensure that the clinical trial is conducted in accordance with the prescribed protocols and SOPs. Monitoring will be carried out by an independent CRA who will not be involved in any other aspect of the trial. In the event that the protocol described herein is revised, the revisions will require approval from the Ministry of Food and Drug Safety and the IRB of DongShin University Gwangju Korean Medicine Hospital.

### Sample size estimation

Because of the lack of adequate preliminary studies and limited research funds, study period, and recruitment opportunities, we have adopted a pilot study design with 18 participants in each group.

### Statistical analysis

A statistician who is not involved in the clinical trial will analyze the final data. We will perform a per-protocol analysis (PP group) for the assessment of efficacy with a supplementary full analysis set (FA group). We will compare the results of analyses between the PP and FA groups and confirm whether there are statistically significant differences between the two groups. If there is a significant difference, the cause will be reviewed and reflected in the efficacy assessment. All statistical analyses will be performed using SPSS version 21 software (IBM Corp.).

Baseline characteristics will be described and compared. Continuous data will be presented as means and standard deviations and compared using the independent *t* test or Wilcoxon rank sum test, while categorical data will be presented as frequencies and percentages and compared using the chi-squared test or Fisher’s exact test.

Changes in scores for the ADAS-K-cog, MoCA-K scale, CES-D, K-ADL scale, K-IADL scale, and EQ-5D-5 L at 8 weeks (at the end of the intervention) and 20 weeks (12 weeks after the end of the intervention), relative to the baseline score, will be analyzed for each group using the paired *t* test or Wilcoxon signed rank test. The degree of changes at each time point will be evaluated using repeated measures analysis of variance and the two-sample *t* test or Wilcoxon rank sum test. Subanalyses will be applied to the statistical analysis according to the participant age. All reported *P* values will be two-sided with confidence intervals at the 95% levels. A *P*value of < 0.05 will be considered statistically significant.

Data for participants who meet the dropout criteria (i.e., < 75% compliance with the protocol procedures [received less than 18 of the 24 scheduled treatment sessions], incidence of SAEs, reluctance to continue the trial, incomplete data that could influence the trial, large error in protocol or significant deviation in implementation, or decision to terminate trial participation by the PI or IRB) will be excluded. Missing values will be implemented by the last observation carried forward method. Interim analyses will not be performed.

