### Hypothesis

The null hypothesis is that the improvement in cognitive function achieved with EA-CCR is not superior to that achieved with CCR in patients with MCI.

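### Efficacy in a superiority trial is judged on the per-protocol set, with partly discretionary post-randomisation exclusions, so the main comparison is open to selection bias of unknown direction

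*Protocol article*

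**What the plan says.** The Hypothesis section sets a superiority question: "The null hypothesis is that the improvement in cognitive function achieved with EA-CCR is not superior to that achieved with CCR in patients with MCI".

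The Statistical analysis section then ranks the analysis sets: "We will perform a per-protocol analysis (PP group) for the assessment of efficacy with a supplementary full analysis set (FA group"). It gives no reason for putting per-protocol (PP) ahead of the full analysis set (FA).

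The same section lists dropout criteria that lead to a participant's data being left out. One is countable: "received less than 18 of the 24 scheduled treatment sessions". Others are "incidence of SAEs, reluctance to continue the trial, incomplete data that could influence the trial". The list ends with "large error in protocol or significant deviation in implementation, or decision to terminate trial participation by the PI or IRB) will be excluded". The sentence does not say which analysis set it applies to.

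The two sets are to be compared in order to "confirm whether there are statistically significant differences between the two groups". If a difference is found, its cause is to be examined and taken into account in judging efficacy. Missing values are to be handled by last observation carried forward (LOCF).

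**The concern.** In a superiority trial, the comparison that randomisation protects is the one between everyone randomised, as allocated. PP gives up part of that protection, because who remains depends on what happened after allocation. Four features of this plan make that more than a formality.

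- **The exclusions are partly discretionary.** No threshold says when an error is large, a deviation significant or missing data influential. The principal investigator (PI) can end a participant's involvement, and under Randomization the PI or the practitioners open the allocation envelopes. Someone who knows the arm can therefore affect who is analysed.
- **The arms are not alike in burden.** Under Interventions, an EA-CCR visit is 30 min of needling plus 30 min of computer work, against 30 min of computer work alone. Only EA-CCR participants are exposed to the needling-related events listed under adverse events. Participants and acupuncturists are unblinded (Discussion).
- **The reach of the exclusion sentence is unclear.** As worded, it does not confine the exclusions to PP.
- **The cross-check is weak.** PP is a subset of FA, so a significance check between them does not compare two independent groups. With at most 36 participants, a non-significant result would reassure little. No fixed rule says how a difference would change the conclusion.

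At stake is the trial's main efficacy estimate, which the Discussion offers as a foundation for further research.

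**Working it through.** **The plan's own figures.** The sample size of 18 per group is fixed on practical grounds, with no effect size, SD, power or dropout rate, so there is no calculation to reproduce. The compliance threshold is consistent: 3 sessions × 8 weeks = 24, and 0.75 × 24 = 18.

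**Inputs for the illustration.** From the article: 18 per arm, two-sided test at 0.05. Assumed, because the article gives neither: the proportion excluded in each arm (q), and the correlation ρ between the tendency to be excluded and the outcome. Outcome means improvement, in SD units, and there is no true effect. Participants with the lowest values of a normal latent score correlated ρ with outcome are excluded.

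**Expected bias.** Among those kept, mean improvement rises by ρ × m(q), where m(q) = φ(z_q)/(1 − q), φ is the normal density and z_q the normal quantile:

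- m(0.05) = 0.1031/0.95 = 0.109
- m(0.10) = 0.1755/0.90 = 0.195
- m(0.20) = 0.2800/0.80 = 0.350
- m(0.30) = 0.3477/0.70 = 0.497

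Bias = ρ × [m(q in EA-CCR) − m(q in CCR)]:

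| Excluded, EA-CCR v CCR | ρ = 0.3 | ρ = 0.5 |
|---|---|---|
| 20% v 5% | 0.3 × 0.241 = 0.07 SD | 0.5 × 0.241 = 0.12 SD |
| 30% v 10% | 0.3 × 0.302 = 0.09 SD | 0.5 × 0.302 = 0.15 SD |
| 5% v 20% | −0.07 SD | −0.12 SD |
| 20% v 20% | 0 | 0 |

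With ρ = 0 the bias is zero whatever the rates.

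**Type I error.** Simulation of the two-sample t test agrees with these biases. In the first two rows, two-sided type I error is about 5.5% to 7%. False claims in favour of EA-CCR, nominally 2.5%, run at about 4% to 6%. With the rates swapped they fall below 2.5%.

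**A harsher case.** Excluding 4 of 18 in EA-CCR and none in CCR gives 0.11, 0.18 and 0.29 SD for ρ = 0.3, 0.5 and 0.8, with type I error of 6.0%, 8.4% and 14.1%. The last value needs a very strong link between exclusion and outcome.

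**Scale.** The standard error of the difference is √(1/n₁ + 1/n₀) SD. With 20% v 5% excluded, the expected numbers are 14.4 and 17.1, so the SE is 0.36. With 30% v 10% they are 12.6 and 16.2, so the SE is 0.38. The largest biases in the table are 0.12/0.36 = 0.33 and 0.15/0.38 = 0.39 of a standard error.

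**Precision, a separate matter.** Losing 20% of 18 leaves about 14 per arm. The effect detectable with 80% power by the two-sample t test then rises from 0.96 SD to 1.10 SD, even if exclusion is unrelated to outcome.

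**The case against.** The strongest objection concerns direction. A reader might infer that the exclusions will favour EA-CCR, because people who tolerate needling badly or fail to improve would leave the analysis. The article does not support that. It gives no dropout rate, no difference between arms and no link between exclusion and response, and lack of improvement is not a listed criterion. The difference in burden supports unequal exclusion, not exclusion related to outcome. CCR participants know they are not receiving EA and might be the ones who leave. In the illustration the sign is an input. This objection stands, and no direction is claimed.

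Second, a reader might infer that randomisation no longer protects anything. That is too strong: an FA analysis is also planned, and the analysing statistician is outside the trial. Being outside the trial is not stated to mean being blinded, however, and FA remains only supplementary.

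Third, the exclusion sentence might be read as stripping the FA set too. The more coherent reading is that the criteria define PP. Otherwise the two sets would largely coincide, and LOCF would have little to act on. What stands is that the wording leaves this open.

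Fourth, the PP and FA comparison may mean only checking whether conclusions agree; no formal test is named. On that reading the step is still not a safeguard, because its result feeds into the efficacy judgement without a fixed rule.

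Finally, this is a small pilot and the illustrated biases are under half a standard error. That lowers the stakes. But the article states a superiority hypothesis, tests at P < 0.05 and aims at preliminary evidence of efficacy.

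**Conclusion.** The concern holds as a weakness in the choice of main analysis set. The choice is stated in the article, so it is not detail left to an unseen plan. The main comparison is open to selection bias because the exclusions follow randomisation, are partly discretionary, and occur in an unblinded trial with unequal burden by arm.

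The size is conditional. Under moderate assumptions it is about 0.07 to 0.15 SD in either direction, with two-sided type I error up to about 7%. It is about zero if exclusion is unrelated to outcome, or equal across arms by the same mechanism. The exclusion rates and correlations are assumptions. The case for change rests on the design argument rather than on any one simulated figure.

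**What to change.** 1. Make the analysis of all randomised participants, as allocated and whatever number of sessions they attended, the primary efficacy analysis.
2. Continue the 8-week and 20-week assessments after treatment stops, where participants agree.
3. State that the dropout criteria define the PP set only.
4. Keep PP as a supportive analysis, with objective exclusions (for example, the 18-session threshold already in the article) fixed before outcomes are seen by arm.
5. Replace the PP-versus-FA significance check with both estimates and their 95% CIs side by side.

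**Cost.** Recruitment has begun, and under Quality assurance a revision needs approval from the Ministry of Food and Drug Safety and the IRB. Participants who stop treatment would need outcome visits. The resulting estimate may be less favourable than the PP one.

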### Study design

The study design is in accordance with the Standard Protocol Items: Recommendations for Interventional Trials (SPIRIT) and Consolidated Standards of Reporting Trials (CONSORT) 2010 guidelines [24, 25] (see Additional file 1). The study is a prospective, outcome assessor-blinded, parallel-arm, single-center (DongShin University Gwangju Korean Medicine Hospital, Republic of Korea), pilot randomized controlled clinical trial with a 1:1 allocation ratio. A total of 36 participants who meet the inclusion and exclusion criteria will be randomly allocated to an EA-CCR or a CCR (*n* = 18 each) group. Participants in the CCR group will receive RehaCom cognitive rehabilitation only, while those in the EA-CCR group will receive EA at Baihui (GV20), Sishencong (EX-HN1), Fengchi (GB20), and Shenting (GV24) along with RehaCom cognitive rehabilitation. The treatment duration will be 8 weeks in both groups. The primary outcome measure will be an improvement in cognitive function evaluated using the Korean version of the Alzheimer’s Disease Assessment Scale-cognitive subscale (ADAS-K-cog). The secondary outcome measures will include changes in scores for the Korean version of the Montreal Cognitive Assessment (MoCA-K) scale, Center for Epidemiological Studies-Depression Scale (CES-D), Korean Activities of Daily Living (K-ADL) scale, Korean Instrumental Activities of Daily Living (K-IADL) scale, and European Quality of Life Five Dimension Five Level Scale (EQ-5D-5 L). All scale scores will be recorded at baseline (before intervention), 8 weeks after the first intervention (i.e., at the end of the intervention), and 12 weeks after completion of the intervention.

This study protocol complies with the principles of the Declaration of Helsinki and Korean Good Clinical Practice guidelines and has been approved by the Ministry of Food and Drug Safety (Medical Device Clinical Trial Plan approval number 859). The trial has been registered at cris.nih.go.kr (registration number, KCT0003415). The study design is summarized in Figs. 1 and 2.

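### Review of a PP/FA discrepancy is triggered only by a significant difference between two overlapping analysis sets, which is a poor guide to whether exclusions changed the efficacy result

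*Protocol article*

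**What the plan says.** All of this is in the Statistical analysis section of the protocol article, unless another section is named.

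- Role of the sets: "We will perform a per-protocol analysis (PP group) for the assessment of efficacy with a supplementary full analysis set (FA group".
- The check: "We will compare the results of analyses between the PP and FA groups and confirm whether there are statistically significant differences between the two groups".
- What follows: "If there is a significant difference, the cause will be reviewed and reflected in the efficacy assessment". No step is stated for the case where the difference is not significant, and no criterion based on the size of the difference is given.
- Level: a P "value of < 0.05 will be considered statistically significant", and P "values will be two-sided with confidence intervals at the 95% levels".
- Exclusions: participants who meet the dropout criteria are left out. One criterion is attendance ("received less than 18 of the 24 scheduled treatment sessions"). Others are SAEs, reluctance to continue, and incomplete data. The article does not define FA, and does not say from which set these participants are removed.
- Tests: the only between-group methods named for change scores are repeated measures ANOVA, the two-sample t test and the Wilcoxon rank sum test. None is assigned to PP versus FA.
- Size (Sample size estimation): "we have adopted a pilot study design with 18 participants in each group".

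**The concern.** Setting PP beside FA should show whether leaving participants out after randomisation has altered the efficacy answer. That can plausibly happen here. Only one arm is needled, participants and acupuncturists are unblinded, and several dropout reasons can depend on treatment or outcome. The plan links its review of the cause to statistical significance between the sets. That trigger has two weaknesses. The sets share most of their members, so a test built for separate groups uses the wrong standard error. And with 18 per arm, a significance test says little about whether a gap matters. A PP estimate well above the FA estimate could then go without the review that the plan intends.

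**Working it through.** **Inputs from the article.** 18 per arm, 1:1; two-sided alpha 0.05; PP leads, FA supplementary. The attendance rule is internally consistent (18/24 = 75%). The sample size rests on feasibility, with no effect size, SD or power, so there is no power figure to reproduce.

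**Assumptions, because the article gives none.** SD of change = 1; PP is a subset of FA; 2 to 9 of 18 excluded per arm; excluded EA-CCR participants 0 to 2.25 SD worse than retained ones.

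**Step 1: standard error within one arm.** With m of 18 retained, PP mean − FA mean = ((18 − m)/18) × (retained mean − excluded mean). Under random exclusion its SD is sqrt(1/m − 1/18). A test that treats the sets as independent uses sqrt(1/m + 1/18).

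| m | true SD | SE if independent | ratio | PP−FA gap needed for P<0.05 | implied retained−excluded gap |
|---|---|---|---|---|---|
| 16 | 0.083 | 0.344 | 4.1 | 0.70 | 6.3 |
| 14 | 0.126 | 0.356 | 2.8 | 0.73 | 3.3 |
| 12 | 0.167 | 0.373 | 2.2 | 0.76 | 2.3 |

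For m = 14 the needed gap is 2.042 × 0.356 = 0.73 SD, and 0.73 × 18/4 = 3.3 SD.

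**Step 2: the two treatment-effect estimates.** With 4 EA-CCR and 2 CCR exclusions (4+2), V_PP = 1/14 + 1/16 = 0.134 and V_FA = 2/18 = 0.111. The true SE of the difference is sqrt(0.134 − 0.111) = 0.151. Treated as independent it is sqrt(0.134 + 0.111) = 0.495. The estimates must differ by 1.96 × 0.495 = 0.97 SD to reach significance. For scale, 18 per arm detects a whole treatment effect of about 0.93 SD with 80% power.

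**Step 3: how often an independent-samples test fires (40,000 simulated trials per scenario).**

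- 4+2, random exclusions: 0, against a nominal 5%.
- 4+2, excluded EA-CCR participants 2.25 SD worse (effect shift 4/18 × 2.25 = 0.50 SD): 0, whether applied within the arm, pooled over arms, or to the effect estimates.
- 6+2, 1.5 SD worse (6/18 × 1.5 = 0.50 SD): 0.07% within the arm, 0.008% pooled, 0.13% on the effect estimates.
- 9+3, 2 SD worse (shift 1.0 SD): 32% within the arm, 26% on the effect estimates, 9% pooled.
- 6+6, with opposite 2-SD shifts in the two arms: 69% on the effect estimates.

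**Step 4: the other reading, comparing the significance verdicts of the two sets.** Among trials with a significantly positive PP result, FA is non-significant, so the check flags, in:

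| PP effect | shift | exclusions | flagged |
|---|---|---|---|
| 0.5 SD | 0.50 SD | 4+2 | 97% |
| 0.5 SD | 0.50 SD | 6+2 | 94% |
| 0.8 SD | 0.50 SD | 4+2 | 88% |
| 0.8 SD | 0.50 SD | 6+2 | 83% |
| 0.8 SD | 0.22 SD (4/18 × 1) | 4+2 | 38% |

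**Step 5: would a correct test rescue the trigger?** A test of retained against excluded participants respects the overlap and holds its 5% level. It detects excluded EA-CCR participants who are 1 SD worse in only 15% (2+2), 30% (4+2), 23% (4+4) and 38% (6+3) of trials. With these numbers a significance trigger is weak even when the test is valid.

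**The case against.** The strongest objection is that the sentence speaks of comparing results of analyses and names no test. It may mean only that each analysis is run in both sets and the verdicts are compared. That reading is open, and Steps 1 to 3 do not apply to it. A reader might infer that the plan prescribes an invalid two-sample test of PP against FA. It does not. The two-sample tests are named two paragraphs later, for changes at each time point. What stands is that the nearest groups named are PP and FA, and that no between-group test named in the section allows for overlap.

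Nor should the verdict reading be dismissed as missing most distortions. Many trials without a disagreement have no positive PP result to protect: with a 0.5-SD PP effect, PP is significantly positive in only 26% (4+2) and 24% (6+2) of trials. Where it is positive and the shift is 0.5 SD, the check usually flags it.

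A reader might also infer that non-significance will be taken as proof of consistency, or that this is the only safeguard. The article says neither. It is silent on what follows non-significance. The supplementary FA analysis and 95% intervals mean that a gap could still be seen.

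The assumed exclusions can be called severe. Last observation carried forward gives zero change to a dropout with no later score, which limits how much worse such participants can look. It does not limit those who attended too few sessions but were assessed. If dropouts leave both sets, PP and FA nearly coincide and the comparison shows still less.

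Finally, this is a pilot. That lowers the stakes, but the article still offers preliminary efficacy evidence as a foundation for further research.

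**Conclusion.** The concern holds in limited form. Statistical significance is the only stated trigger for reviewing a PP/FA discrepancy, and it suits the purpose badly. On the literal reading, an independent-samples test of overlapping sets would almost never fire: about 0 to 0.1% at a 0.5-SD shift with 4 to 6 EA-CCR and 2 CCR exclusions. It becomes appreciable only under extreme exclusion, about 30% with 9 of 18 at 2 SD worse. On the verdict reading the check works for large shifts and fades for small ones (38% at 0.22 SD). On neither reading does it measure the size of the discrepancy.

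The standard-error ratios follow from the overlap alone and do not depend on the SD. The firing rates rest on assumed normal scores, exclusion counts and shifts. The subset relation is inferred from the usual meaning of PP and FA. Which set should lead is a separate question. The plan should be changed, but the present wording does not by itself show that a distorted result would be accepted.

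**What to change.** In the Statistical analysis section, delete the test for significant differences between PP and FA and the condition attached to it. Replace them with three commitments:

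1. The between-arm difference in ADAS-K-cog change, with its 95% CI, is reported side by side for FA and PP.
2. The number of exclusions and the reasons for them are reviewed and reported by arm, whatever the P value.
3. The efficacy conclusion states any material difference in direction or size between the two estimates.

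If a numerical threshold for a material difference is wanted, the sponsor should choose it in advance. If a formal measure is wanted, give a 95% CI for (PP estimate − FA estimate) from a bootstrap that resamples participants within arm and recomputes both estimates each time, so that the overlap is respected. One sentence defining FA, and saying from which set dropouts are removed, would settle the remaining ambiguity.

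The cost is wording and one extra table, with no added participants, visits or staff. The small downside is that discrepancies must be discussed more often.
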